### 2.3. Intervention

Prior to the commencement of the FINE program, a process of development of the frailty intervention module and education materials will be conducted. The educational materials will be developed based on the frailty intervention module to serve as a reference or reading materials for the respondents throughout the program. It includes flipchart, PowerPoint slides, booklet, and posters. During a 12-week (3-month) intervention period, in overall, participants attend one session of frailty, exercise, and healthy eating talk; 20 sessions of a low to moderate intensity multi-component exercise course; and 5 sessions of nutrition education intervention. Additionally, there is one session during the following 3 months after the intervention ends. It should be noted that each session will be held in the facility area or hall of the PPR flats for around 60 min.

As an introduction, a few talk sessions and an exercise demonstration will be conducted for few days of the first week regarding frailty, exercise, and nutrition with the aims of introducing, refreshing, and improving the knowledge regarding the topic. Each topic will be delivered by the research team based on the frailty intervention module. In the following week, the exercise activities will be conducted two days per week [19] concurrently with the nutrition session, which is only once per week. The multicomponent exercise program is an adaptation with a slight modification of the frailty intervention study conducted by Tarazona-Santabalbina, which involves a progressive combination of activities including proprioception and balance exercises, aerobic training, resistance training, and stretching [29]. All exercise sessions will be delivered in group as it is effective in reducing or postponing frailty [46] and will be supervised by qualified physiotherapists [29]. For nutrition education intervention, five sessions of group discussion are conducted among participants; the main idea being to educate the elderly to improve their intake of calories, protein [47,48], calcium, and vitamin D [49]. Thus, every week they will receive an explanation about the importance of each nutrient, its sources, and the recommendation for daily intake. The session will also be interspersed with a few quizzes and hands-on activities, such as cooking practice [18] and games [50], to reinforce the learning objectives. In the following 12 weeks after the intervention ends, one session is added with the purpose of doing revision regarding the previous education session and to supervise the exercise routine practice by the elderly. The session will be conducted at week 6 after the intervention ends and will be delivered by a dietitian and a physiotherapist from the research team, lasting for one hour. The respondents in the control group will not receive any intervention program. A summary of the FINE program is shown in Table 2.

### 2.4. Outcome Measures

In this research study, the primary and secondary outcomes will focus on three key domains, which are physical changes, cognitive performance, and functional improvement. This includes the changes in frailty status and score, knowledge, attitude, and practice (KAP) towards frailty, nutrition and exercise, dietary intake, anthropometric measurements, cognitive status, functional ability status, mobility status, and risk of falls. Apart from that, demographic data (e.g., gender, race, age, monthly income, education level, and marital status) will be assessed as well.

#### 2.4.1. Primary Outcome

##### Frailty Score/Status

The frailty status will be assessed using the well-established Malay language standardized phenotype of the frailty questionnaire; as proposed by Fried et al. [5]. The questionnaire evaluates five components of the frailty syndrome (weight loss, exhaustion, weakness, slowness, and low activity) and allocates one point for each criterion met; respondents meeting zero criteria are defined as non-frail, whereas those meeting one or two criteria are defined as pre-frail, and those meeting three, four, or five criteria are defined as frail.

#### 2.4.2. Secondary Outcomes

##### Knowledge, Attitude, and Practice (KAP) towards Frailty, Nutrition, and Exercise

The KAP questions will be developed prior to data collection to measure the construct of knowledge, attitude, and practice in relation to frailty, nutrition, and exercise among the elderly. The questions will consist of items based on the content of the developed educational materials. A validation and reliability study will be conducted after it is developed.

##### Dietary Intake

The amount of food items consumed by the respondents in the past week will be recorded by the validated Malay language of Diet History Questionnaire (DHQ) via the interview method. The data will be analyzed using the Nutritionist Pro™ Diet Analysis Software and then compared to the Malaysian Recommended Nutrient intake [51].

##### Anthropometric Measurements

Body weight will be measured using an electronic flat scale (SECA 803, Hamburg, Germany).Height of the participant will be measured using stadiometer (SECA 213, Hamburg, Germany).When no valid measurement can be obtained due to particularities (e.g., kyphosis, scoliosis), an alternative method will be used to measure the height using a demi-span measurement. The height will be measured using equations developed for the Malaysian elderly [52].Body Mass Index (BMI) will be derived using the calculation: weight in kilograms divided by the height in meters squared [weight (kg)/height^2^ (m^2^)] [53]Body part circumference including mid-upper arm circumference (MUAC) and calf circumference (CC) will be measured using a flexible non-stretchable measuring tape (SECA 201, Hamburg, Germany) [52].Body composition including body fat percentage and muscle percentage will be assessed using a portable body composition analyzer (OMRON HBF-375, Japan).

##### Cognitive Status

This study will use the validated Malay language version of the Mini-Mental State Examination (M-MMSE) questionnaire to assess the cognitive functioning of the respondents [54].

##### Functional Ability

The well-established Malay language version of the Lawton Instrumental Activities of Daily Living (IADL) questionnaire will be used to assess the respondents’ ability to perform eight daily activities (i.e., ability to use telephone, shopping, preparing meals, housekeeping, doing laundry, using public transport, taking medications, and handling finances) [1,15].

##### Mobility Status

A well-established Malay language version of the Short Physical Performance Battery (SPPB) will be used for this study to test the respondents’ mobility status [55] to evaluate lower limb extremity functioning in three components (balance test, gait speed test, and repeated chair stand test).

##### Risk of Falls

The Malay language version of the Berg Balance Scale (BBS) will be used to assess the risk of falls among the respondents [56]. A process of back translation and monolingual testing will be conducted for the questionnaire prior to the evaluation process [57].

### 2.5. Statistical Analysis

The description of the respondents’ characteristics will be reported by group (control and intervention). Depending on the distribution of the variable of interest, the descriptive statistics of continuous data will be presented by using the mean and standard deviation and the median and the inter-quartile range. Categorical data will be presented as frequencies and percentages. For primary analysis, since there are small number of cluster, as recommended by Hayes and Moulton (2017), analysis will be conducted at cluster level instead of individual level [58]. Thus, the primary and secondary outcomes will be compared within and between groups using 2-way repeated ANOVA by general linear model. Any covariate data at baseline value will be adjusted and further test will be conducted using a repeated measure analysis of covariance (ANCOVA). If the data is not distributed normally, Kruskall–Wallis test will be used to analyze the data. Statistical significance is set at *p* < 0.05. Data will be entered and analyzed using SPSS 25.0 software.

Intention-to-treat (ITT) will be applied in the data management and analysis. All data will be processed according to their arm even if the participant did not manage to come to all the intervention sessions. It is assumed that majority of the participant in the intervention arm will receive adequate number of the intervention sessions. Action will be taken in order to prevent lower attendance from the participants such as conducting extra exercise classes for participants who could not come to a certain session. For every nutrition session, class will start with the revision on the topic that had been discussed in previous session. This can help participants who could not come to the previous nutrition session to learn the topic they missed.

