### 2.1. Trial Design

The “FINE” project is a 3-month (12 weeks) intervention program, single-blind, two-armed cluster randomized controlled trial (cluster RCT), conducted among pre-frail elderly with a pre- and post-intervention and 3-month follow-up assessments to assess the effectiveness of the program. The trial mainly comprises nutritional education and exercise intervention among older people aged 60 years and above in the PPR flats in Kuala Lumpur. The trial is registered prospectively at ClinicalTrial.gov with registration number NCT04327544 on 30 March 2020.

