#### 2.2.4. Sample Size Calculation

The sample size for each arm was calculated by using two group mean comparison formula [25]. Both the mean and standard deviation from the study conducted by Tarazona-Santabalbina et al. [29] in Spain was used as the reference, and based on the calculation using the result for the variable of the Short Physical Performance Battery (SPPB), the sample size required for each intervention and control arm is 15 respondents.

With a hypothesized intra-cluster correlation coefficient (ICC) 0.02 [1], fixed cluster size of 4 [45], and a minimum of 15 respondents required under individual randomization, the calculated minimum required cluster size and sample size is 4 and 16 per arm, respectively. After an adjustment for the estimated response rate, a sample size of 30 respondents per arm is required to provide of 80%, with α = 0.05. In total, the respondents for both arms are 60 elderlies with approximately 8 respondents from each cluster (4 clusters for each arm).

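### The cluster-level repeated ANOVA compares change in flat summaries and makes inefficient use of each participant's own baseline; adjusting for it before averaging is more precise and more robust to missed visits

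*Protocol article*

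**What the plan says.** Section 2.5 (Statistical Analysis) says that, because clusters are few, the primary "analysis will be conducted at cluster level instead of individual level [58]. Thus, the primary and secondary outcomes will be compared". The method is given as outcomes "compared within and between groups using 2-way repeated ANOVA by general linear model". A following sentence says that baseline covariates will be adjusted for in a further repeated-measures ANCOVA. It does not name the baseline value of the outcome as a covariate, nor say whether adjustment is made on participants or on flats.

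Section 2.1 (Trial Design) describes one cohort "with a pre- and post-intervention and 3-month follow-up assessments to assess the effectiveness of the program". Section 2.2.4 (Sample Size Calculation) gives the numbers: "In total, the respondents for both arms are 60 elderlies with approximately 8 respondents from each cluster (4 clusters for each arm").

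The intention-to-treat paragraph of section 2.5 concerns session attendance: "All data will be processed according to their arm even if the participant did not manage to come to all the intervention sessions". The article does not say how a flat's value at a visit is formed when someone misses that assessment.

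**The concern.** A repeated ANOVA on flats takes one value per flat per visit, and its group-by-time term compares how those values change. Two things follow.

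The first holds however the flat values are built. Change from baseline is usually a less precise contrast than follow-up adjusted for baseline, because it subtracts the whole baseline value even when baseline predicts follow-up only partly. With four flats per arm, precision is scarce. Adjusting afterwards on flat averages spends a flat-level degree of freedom; adjusting on participants before averaging does not.

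The second holds only on one reading. If a flat's value is the mean of those seen at each visit, a flat of about eight people can shift because of who is absent. If frailer people are absent more often, the planned within-group comparison shows a gain that nobody experienced. If that pattern also differs by arm, the arm comparison is biased. Unequal loss is plausible: one arm is offered 20 exercise sessions and 5 nutrition sessions as well as talks, and the other receives no programme.

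**Working it through.** **1. The plan's own figures.** Section 2.2.4 gives ICC 0.02, cluster size 4 and 15 per arm under individual randomisation. Design effect = 1 + (4 - 1) × 0.02 = 1.06; 15 × 1.06 = 15.9, so 16 per arm in 4 flats. This reproduces. The 16 is raised to 30 for a response rate that is not stated: 16/30 = 53%. If that rate means retention, the plan tolerates up to 47% loss, or 60/8 = 7.5 people per flat falling to 32/8 = 4.

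**2. Precision with nobody lost.** Let follow-up SD be σ, baseline SD be kσ, and within-person correlation be r. Per-person variance:
- change: σ²(1 + k² - 2kr)
- follow-up adjusted for own baseline: σ²(1 - r²)
- proportional cut: (k - r)² / (1 + k² - 2kr), which is (1 - r)/2 when k = 1.

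With k = 1: r = 0.7 gives 15%, r = 0.6 gives 20% and r = 0.3 gives 35%. Simulation with eight flats and ICC 0.02 gives about 15% to 34% over the same range. At r = 0.6, two separate simulations gave standard errors (change v adjusted, SD units) of 0.224 v 0.204 and 0.230 v 0.207; the cuts are 1 - (0.204/0.224)² = 17% and 1 - (0.207/0.230)² = 19%.

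The gain depends on k. If the baseline frailty score keeps to the eligibility range of 1 or 2, its SD is at most about 0.5. If follow-up SD were 1.0 (assumed), k = 0.5 and the cut is 0.04/0.95 = 4% at r = 0.3, zero at r = 0.5 and 0.04/0.55 = 7% at r = 0.7. The 15% to 34% therefore applies to outcomes with similar spread at both visits.

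**3. Degrees of freedom.** Four v four flats leave 4 + 4 - 2 = 6. A flat-level baseline covariate leaves 5. Own-baseline adjustment on about 60 people leaves 6.

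**4. Missed visits, if flat means are taken over those seen.** A flat of eight with four people at score 1 and four at 2 (assumed mix) has mean 1.50. If two of the 2s are absent and nobody changes, the mean is (4 × 1 + 2 × 2)/6 = 1.33, a false gain of 0.17.

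Simulation with no treatment effect, 30 per arm, r = 0.6, and absence rising with baseline at log-odds 0.8 per SD (all loss settings assumed):

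| Loss by arm | Flat means of those seen | Mean within-person change | Own-baseline residuals |
|---|---|---|---|
| 30% v 10% | -0.09 SD | about +0.05 SD | about 0 |
| 47% v 20% | -0.10 to -0.11 SD | about +0.07 to +0.08 SD | about 0 |

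Equal 47% loss gives a false within-arm fall of about 0.19 SD and no arm difference. Type I error of the flat-mean comparison in the two unequal scenarios is about 5.5% to 6%.

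**5. Limit of the remedy.** If absence depends on frailty at the time of the visit, the own-baseline method is itself biased by about -0.09 SD (30% v 10%) and -0.12 SD (47% v 20%).

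**The case against.** The strongest reply is that the article never says flat means are taken over whoever attends. Values built from completers, or from mean within-person change, fit the wording equally well, and handling of missed visits is commonly left to a fuller document. That stands. A reader might infer that baseline and follow-up means come from different people, or that the plan as written lets a flat improve when nobody changed. The documents do not support either: section 2.1 describes one cohort, so those seen later are a subset of those seen at baseline, and with full retention the effect is exactly zero. Cluster-level analysis does not cause it; loss does.

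It is also fair that the harm to the arm comparison is small, about 0.1 SD against standard errors of roughly 0.27 to 0.36 SD under loss. Larger false-positive rates (11% to 30%) arise only if nobody's score varies at all, with score-related loss in one arm and random loss in the other. Random loss, or loss of the same pattern in both arms, leaves the arm test valid.

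The objection that baseline adjustment is already planned stands only in part. The ANCOVA sentence neither names the baseline outcome nor places the adjustment at person level.

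The precision argument survives these replies, because it does not depend on loss or on how flat values are formed.

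**Conclusion.** The point holds as one of efficiency, with a conditional point on bias. The stated repeated ANOVA compares change in flat summaries, and adjusting for own baseline before averaging reduces the variance of the arm difference by about 15% to 34% with full retention, assuming correlation 0.7 to 0.3 and equal SD at both visits. For the frailty score the gain may be much smaller if baseline is confined to 1 or 2. If flat summaries are taken over those seen, baseline-related loss biases the within-group comparison, and biases the arm comparison by about -0.1 SD only if it differs by arm. Mean within-person change does not cure this; it reverses the sign. Correlations, loss rates and selectivity are all assumptions, since the article gives none. It is a worthwhile improvement and does not invalidate the choice of a cluster-level analysis.

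**What to change.** Keep the flat as the unit of inference and replace the repeated ANOVA on flat summaries. For each follow-up visit:
1. regress the outcome on the participant's own baseline value, all participants pooled, with no arm term;
2. average the residuals of those seen at that visit within each flat;
3. compare the flat means between arms.

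State also that this is where the baseline outcome is adjusted, so that the ANCOVA sentence is not read as a flat-level covariate.

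The cost is revised wording, one extra analysis step and a few lines of code, using baseline data already collected. The estimate becomes conditional on baseline. The method removes bias from loss related to measured baseline, not from loss related to unobserved later frailty. The 6 degrees of freedom hold only if flats are the randomised units. Section 2.2.5 places randomisation at the level of the two selected zones, and that must be reconciled separately.

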## Figures and Tables

**Figure 1 nutrients-12-02758-f001:**
[figure not shown]
The overview of the frailty intervention study flow. Adapted from the CONSORT 2010 flow diagram (extension to cluster randomized trails) [41].

**Table 1 nutrients-12-02758-t001:** The summary of the inclusion and exclusion criteria for the Frailty Intervention through Nutrition Education and Exercise (FINE) program.

Inclusion Criteria	Exclusion Criteria
Men or women aged 60 years and above	Self-reported chronic diseases and mental illnesses (heart-related disease, chronic obstructive pulmonary disease (COPD), stroke, cancer, asthma, renal dysfunction, terminally ill, major depression, bipolar, disorder, obsessive compulsive disorder and post-traumatic disorder)
Meet one or two frailty phenotype score (pre-frail)	Physical Activity Readiness-Questionnaire (PAR-Q & YOU)(Yes ≥ 1) [43]
Able to ambulate without personal assistance	Bedridden
Residing in the PPR flats in Kuala Lumpur	Cognitive impairment (Elderly Cognitive Assessment Questionnaire, ECAQ < 6) [44]
Willing to participate in the intervention program with informed consent	Sensory impairment (visual & hearing) that will interfere with communication
	Unable to read and write
	Already involved or still participating in any health interventional study
	Any sustained fracture (hip, vertebrae) in past six months
	Any surgery (hip, abdominal area) in past six months

**Table 2 nutrients-12-02758-t002:** Summary of the frailty FINE program.

Intervention Group					Control Group
12 weeks intervention program	**Week**	**Day 1**	**Day 2**	**Day 3**	* No intervention
	1	Talk on frailty	Talk on exercise	Talk on healthy eating	
	2	Multicomponent exercise *			
	3	Multicomponent exercise *		Nutrition education class	
	4	Multicomponent exercise *			
	5	Multicomponent exercise *		Nutrition education class	
	6	Multicomponent exercise *			
	7	Multicomponent exercise *		Nutrition education class	
	8	Multicomponent exercise *			
	9	Multicomponent exercise *		Nutrition education class	
	10	Multicomponent exercise *			
	11	Multicomponent exercise *		Nutrition education class	
	12	INTERVENTION END			

* exercise intervention.

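### The primary outcome is a score/status pair compared within and between arms over three visits, and no measure, visit or model term is named as the deciding test

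*Protocol article*

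**What the plan says.** Section 2.4.1 gives the primary outcome the single label "Frailty Score/Status". It describes a count of five criteria (0 to 5) and a three-category class derived from that count. Section 2.4 lists "the changes in frailty status and score" among the outcomes and ranks neither.

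Section 2.1 describes a trial "with a pre- and post-intervention and 3-month follow-up assessments to assess the effectiveness of the program". That makes three visits, none of them called primary.

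Section 2.5 says that because clusters are few, "analysis will be conducted at cluster level instead of individual level", and that "the primary and secondary outcomes will be compared within and between groups using 2-way repeated ANOVA by general linear model". It then adds: "Any covariate data at baseline value will be adjusted and further test will be conducted using a repeated measure analysis of covariance (ANCOVA)". A Kruskal-Wallis test replaces these if the data are not normal. Significance is p < 0.05 throughout.

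Table 1 admits only people who meet one or two phenotype criteria, that is, the pre-frail class.

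**The concern.** A 2-way repeated ANOVA produces three tests: group, time and group-by-time. The plan does not say which one answers the trial's question. With two primary measures, three visits, within-arm comparisons, an additional ANCOVA and a fallback rank test, a favourable p-value could come from several places, each judged at 0.05.

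Three features make this more than a matter of tidiness:

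- **Within-arm tests.** Participants enter because their score is 1 or 2. Change in one arm can reflect regression to the mean, in a direction that depends on the source population, or repeat testing. It is not evidence that the programme works.
- **Status.** Everyone is pre-frail by eligibility, so status is essentially constant at baseline, apart from drift between screening and the baseline visit. A baseline level of status carries almost no information.
- **The group term.** It averages over every visit in the model. If baseline is one of them, the average includes a visit at which no effect can exist.

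At stake are the false-positive rate of the primary claim and, depending on which term is read, the trial's power.

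**Working it through.** **Inputs from the protocol article.** Section 2.2.4 gives 15 per arm under individual randomization, ICC 0.02, cluster size 4, 4 flats per arm, 30 per arm finally (about 8 per flat), 80% power and α = 0.05. Section 2.1 gives three visits.

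**The plan's own figure.** Design effect = 1 + (4 − 1) × 0.02 = 1.06. Then 15 × 1.06 = 15.9, rounded up to 16 per arm, and 16 / 4 = 4 flats per arm. This reproduces.

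**Assumptions.** The effect size behind the 15 is not given. A standardized difference of about 1.03 matches 15 per arm at 80% power (0.805 by the normal formula), so 1.03 SD is used here. That calculation rests on the SPPB, so its use for frailty score is illustrative. The test is taken as two-sided. Between-visit correlation is assumed to be 0.5, with range 0.3 to 0.7.

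**Step 1: false positives from two terms of one model.** For two independent tests, 1 − 0.95² = 0.0975. Simulating flat means (4 v 4 flats, ICC 0.02, no effect, 40,000 runs) and accepting either the group or the group-by-time term gives 9.5% to 9.8%. Each term alone holds about 5%.

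**Step 2: dilution of the group term.** In a balanced model the group main effect is the mean of the visit-specific differences. Let the difference be 0 at baseline and δ at the post-intervention visit:

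- effect sustained at follow-up: (0 + δ + δ)/3 = 0.67δ
- half lost by follow-up: (0 + δ + 0.5δ)/3 = 0.50δ
- present only at the post visit: (0 + δ + 0)/3 = 0.33δ

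Without the baseline level these become 1.00δ, 0.75δ and 0.50δ.

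**Step 3: what this does to power** (effect 1.03 SD, correlation 0.5). The last column is the two-stage baseline-adjusted test at the post-intervention visit.

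| Effect pattern | Per flat | Group term | Group-by-time term | Two-stage test |
|---|---|---|---|---|
| Sustained | 4 | 49% | 73% | 76–77% |
| Sustained | 8 | 75% | 95% | 95% |
| Post visit only | 8 | 27% | 95% | 95% |

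The gap between the group and group-by-time terms depends on the correlation. For a sustained effect with 4 per flat it is 58% v 58% at correlation 0.3 and 42% v 92% at 0.7.

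At 8 per flat and correlation 0.5, the same written plan therefore has power anywhere from 27% to 95%, depending on which unnamed term is read and how long the effect lasts.

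**The case against.** A reader might infer that the planned ANOVA dilutes the effect and wastes power outright. The documents do not support that. Section 2.5 never says that the group main effect decides. The group-by-time term, which many analysts would read as the treatment test, is not diluted, and at correlation 0.5 its power is close to that of the baseline-adjusted test. That baseline is a level of the time factor is also inferred, from the three visits and the within-group comparison. The ANCOVA sentence may be meant to adjust for the baseline outcome, although its wording leaves this open.

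A reader might also put the error rate at 18.5%, from four independent tests (score and status at two visits): 1 − 0.95⁴ = 0.185. Section 2.5 does not list four such tests, and independence cannot hold, because status is a grouping of the score and visits repeat on the same people. An illustrative simulation with those dependencies gives about 13% to 14%.

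It can further be said that *within and between* merely names the two factors of a mixed ANOVA, and that an unseen analysis plan may name the primary contrast. The first is possible, but the sentence presents both as outcome comparisons. On the second, the article does fix a two-variable primary outcome and a within-and-between comparison, so these are stated choices and not only omitted detail.

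Finally, section 2.2.5 places randomization at zone level with two zones. This stands as a limit on the power figures and on any 4 v 4 flat comparison. It does not affect the point that no test is named.

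**Conclusion.** The point holds in this form: the primary outcome is a pair, observed at three visits and compared within and between arms, with no single deciding test.

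The firmest number is the type I error of about 10% if either the group or the group-by-time term may carry the claim. The score/status pair and within-arm tests add routes whose exact cost depends on correlations that the article does not give. Dilution to between one third and two thirds is conditional: it applies only if baseline is a time level and the group main effect is the treatment test. The group-by-time term escapes dilution, but as a 2-df omnibus test it still needs a further contrast to say when, and in which direction, the arms differ.

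The power figures are illustrative. They rest on an assumed effect of 1.03 SD, an assumed between-visit correlation, and flats as the randomized units, as section 2.2.4 assumes. The conflict with the zone-level allocation in section 2.2.5 must be reconciled separately. The point should be corrected before analysis, since it bears on how the primary claim is decided.

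**What to change.** In sections 2.4.1 and 2.5, name one primary measure, one visit and one between-arm contrast. For example: the difference in frailty score at the end of the intervention, adjusted for the participant's own baseline score, by the two-stage cluster-level method. Regress the score on its baseline value ignoring arm, average the residuals within each flat, and compare the flat means between arms. This keeps the cluster-level approach that section 2.5 already adopts. The 4 v 4 comparison is valid only once flats are confirmed as the units randomized.

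Make status, the follow-up visit and within-arm changes supportive, with within-arm changes reported descriptively. Analyse status without a baseline level.

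The cost is wording; no new data are needed. The downside is that status and follow-up results become secondary. The Discussion (section 3) describes the main aim in terms of frailty status, so the sponsor may reasonably prefer status, or another visit, as primary. What matters is that the choice is single and fixed in advance.

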## Abstract

The ageing process has been associated with various geriatric issues including frailty. Without early prevention, frailty may cause multiple adverse outcomes. However, it potentially may be reversed with appropriate interventions. The aim of the study is to assess the effectiveness of nutritional education and exercise intervention to prevent frailty among the elderly. A 3-month, single-blind, two-armed, cluster randomized controlled trial of the frailty intervention program among Malaysian pre-frail elderly will be conducted. A minimum of total 60 eligible respondents from 8 clusters (flats) of Program Perumahan Rakyat (PPR) flats will be recruited and randomized to the intervention and control arm. The intervention group will receive a nutritional education and a low to moderate multi-component exercise program. To date, this is the first intervention study that specifically targets both the degree of frailty and an improvement in the outcomes of frailty using both nutritional education and exercise interventions among Malaysian pre-frail elderly. If the study is shown to be effective, there are major potential benefits to older population in terms of preventing transition to frailty. The findings from this trial will potentially provide valuable evidence and serve as a model for similar future interventions designed for elderly Malaysians in the community.

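### Open-ended baseline adjustment in a cluster-level ANCOVA on eight flats: each flat-level covariate costs one of six error degrees of freedom, and the plan sets no limit

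*Protocol article*

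**What the plan says.** Section 2.5 (Statistical Analysis) gives the small number of clusters as the reason that "analysis will be conducted at cluster level instead of individual level". The primary and secondary outcomes are to be "compared within and between groups using 2-way repeated ANOVA by general linear model". The adjustment rule follows directly: "Any covariate data at baseline value will be adjusted and further test will be conducted using a repeated measure analysis of covariance (ANCOVA"). The section gives no list of covariates, no maximum number, and no individual-level step before the flats are compared. The threshold is "Statistical significance is set at *p* < 0.05", with sidedness not stated.

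Section 2.2.4 (Sample Size Calculation) plans "approximately 8 respondents from each cluster (4 clusters for each arm"), and the Abstract agrees: "A minimum of total 60 eligible respondents from 8 clusters (flats) of Program Perumahan Rakyat (PPR) flats will be recruited". Section 2.1 describes a trial "with a pre- and post-intervention and 3-month follow-up assessments", so there are three time points.

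Section 2.4 (Outcome Measures) says that "demographic data (e.g., gender, race, age, monthly income, education level, and marital status) will be assessed as well". It also names knowledge, attitude and practice, diet, anthropometry, cognition, function, mobility and risk of falls among the outcomes to be assessed for change, so these are measured at baseline too.

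**The concern.** A cluster-level analysis of eight flats has eight observations at each time point. After the two arm means are fitted, six degrees of freedom remain to estimate the error. Each covariate entered as a flat mean or proportion takes at least one of them. A categorical variable such as race or marital status takes more if it is coded in several levels.

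The plan chooses the cluster level because clusters are few, and then states an adjustment rule with no upper bound. The two do not fit together. An analyst who follows the rule must stop at a number of covariates that the plan does not give, and that choice drives the critical value. At stake is the usefulness of the adjusted result: with a few covariates it loses much of its power, and with six or more it cannot be tested at all.

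**Working it through.** **Inputs.** Eight flats, four per arm (Abstract; 2.2.4). Three time points (2.1). ICC 0.02, cluster size 4, 15 per arm before clustering, 80% power and α = 0.05 (2.2.4). Two-sided testing is assumed.

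**The plan's own figure.** Design effect = 1 + (m − 1) × ICC = 1 + 3 × 0.02 = 1.06. Then 15 × 1.06 = 15.9, rounded up to 16, and 16 / 4 = 4 clusters per arm. The stated 16 respondents and 4 clusters per arm are reproduced. The 15 cannot be checked, because the mean and SD behind it are not given.

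**Error degrees of freedom.** Between flats: 8 flats − 2 arms − k covariates = 6 − k. For the arm-by-time test with three time points, if covariate-by-time terms are fitted: (3 − 1) × (6 − k), which is 12 with none, 10 with one and 0 with six. A rank check confirms this: with six covariates the design matrix has rank 8, the residual sum of squares is 0, and no F or p-value exists.

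**Assumed effect.** The article states no effect size. Under the normal approximation, 15 per arm at 80% power implies d = √(2/15) × (1.960 + 0.842) = 1.02. Because 15 is a rounded-up number, d could be as high as √(2/14) × 2.802 = 1.06. This refers to the SPPB, which is a secondary outcome, and not to the primary frailty outcome.

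**Power.** Variance of a flat mean, in SD² units: v = [1 + (m − 1) × 0.02] / m. Standard error of the arm difference: √(2v/4). Noncentrality: d / SE.

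- m = 4 analysed per flat (16 per arm): v = 1.06/4 = 0.265, SE = 0.364, noncentrality 1.023/0.364 = 2.81.
- m = 7.5 per flat (60/8): v = 1.13/7.5 = 0.151, SE = 0.274, noncentrality 3.73.

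Power comes from the noncentral t with 6 − k df, with covariates that explain nothing:

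| k | df | critical t | power, m = 4 | power, m = 7.5 |
|---|---|---|---|---|
| 0 | 6 | 2.45 | 65% | 87% |
| 1 | 5 | 2.57 | 62% | 84% |
| 2 | 4 | 2.78 | 57% | 79% |
| 3 | 3 | 3.18 | 49% | 70% |
| 4 | 2 | 4.30 | 35% | 52% |
| 5 | 1 | 12.7 | 18% | 23% |
| 6 | 0 | none | not estimable | not estimable |

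At d = 1.06 the same calculation gives, for k = 0 to 5, 68, 65, 59, 51, 37 and 18% (m = 4) and 89, 87, 82, 73, 54 and 24% (m = 7.5). The pattern does not depend on which value is taken.

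**Two limits of the table.** A covariate that predicts the outcome would recover some of the loss. In the other direction, the table leaves out chance correlation between covariates and arm. With independent normal covariates on eight flats, a simulation gave a median variance inflation for the arm effect of 1.09, 1.30, 1.71, 2.40 and 4.08 for k = 1 to 5.

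**The case against.** The strongest reply is that the article never says how many covariates will enter. A reader might infer from Section 2.4 that all six demographic variables go into the ANCOVA, so that the planned model has zero error df. The article does not support that: it says only that these variables will be assessed, and gives them as examples. The adjustment sentence could also mean whichever covariates are judged relevant. Zero df is therefore the end point of the most literal reading and not a stated plan. This part of the objection stands.

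Three further points also stand. With one covariate the cost is small, and the outcome's own baseline value would normally repay it. The ANCOVA is described as a further test, so the unadjusted repeated ANOVA keeps its degrees of freedom; a reader who concludes that the whole primary analysis cannot be fitted goes too far. The tabulated critical t values belong to a between-flat comparison; the omnibus arm-by-time test has twice the error df.

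A reader might also infer that covariates will be picked after seeing baseline imbalance, or that the adjusted model will be moved to individual level and ignore clustering. The text states neither.

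The last reply is that covariate lists are commonly left to a statistical analysis plan. That is true of a missing list. Here the article states a rule, without a bound, that works badly with the unit of analysis chosen in the same paragraph. That remains a fault of the text as written.

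**Conclusion.** The concern holds in a limited form. With the flat as the unit, each flat-level covariate uses one of six error df, and Section 2.5 sets no limit. One covariate is acceptable, three to five make the adjusted test weak or close to useless, and six or more leave nothing to test with.

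The df and critical values are exact. The power figures are illustrative: they rest on an effect of 1.02 to 1.06 SD inferred for the SPPB, ICC 0.02, two-sided 5% testing, and covariates that neither explain the outcome nor correlate with arm.

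The six df themselves assume that the flat is the randomized unit. Section 2.2.5 describes randomization at zone level with two zones. Whether six df are valid under that design is a separate issue, and the present point does not depend on how it is settled.

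**What to change.** Delete the open-ended adjustment sentence in Section 2.5 and name a short list now: the outcome's own baseline value, age and sex. Then use the two-stage method for few clusters:

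1. Regress the individual outcome at the post-baseline assessment on the listed covariates, leaving out the arm term.
2. Average the residuals within each flat and compare the eight means between arms by a t-test on 8 − 2 = 6 df.

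This keeps the cluster-level choice that the plan has already made. Individual-level covariates are adjusted without taking degrees of freedom from the comparison of flats.

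Do not put zone in the list. As Section 2.2.5 reads, zone coincides with arm, so a first-stage regression on zone would remove the arm effect before it is tested.

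The cost is a change of wording and slightly more analysis work, with no change to recruitment, visits or measurements. The downside is that covariates outside the list are not adjusted for.
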